## Abstract

**Background:**

Proximal gastrectomy has gradually gained more attention due to its superiority in retaining the function of part of the stomach. The inevitable loss of the antireflux barrier and postoperative complications resulting from proximal gastrectomy can severely affect the quality of life. Continuous improvements in digestive tract reconstruction after proximal gastrectomy have yielded the development of a variety of methods with antireflux functions. Recently, our center attempted the left-open single-flap technique and initiated a multicenter, prospective, randomized controlled trial for patients undergoing proximal gastrectomy to reduce the difficulty of surgical anastomosis and the incidence of perioperative complications compared with the double-flap technique. These findings will provide more evidence-based medical research for the development of clinical guidelines.

**Methods/design:**

This study is a prospective, multicenter, randomized controlled clinical trial. We plan to recruit 250 patients who are eligible for proximal gastrectomy. After informed consent is obtained, patients will be randomly assigned to the trial group (left-open single-flap technique) and the control group (double-flap technique) in a 1:1 allocation ratio.

**Discussion:**

Increasingly, clinical studies have focused on the improvement of reconstruction modalities after proximal gastrectomy. Among these methods, the double-flap technique is a clinically effective method. The purpose of this study is to establish a prospective randomized controlled trial to compare the efficacy of the left-open single-flap technique versus the double-flap technique after proximal gastrectomy, aiming to provide more evidence-based medical studies for digestive tract reconstruction in proximal gastrectomy.

**Clinical Trial Registration:**

ClinicalTrials.gov, identifier [NCT05418920].

## Introduction

Despite the decreasing incidence and mortality of gastric cancer in recent years, the incidence and proportion of proximal early gastric cancer has markedly increased (1). However, the choice of an appropriate surgical procedure, the only radical treatment for this condition, has been controversial (2). Currently, proximal gastrectomy has gradually gained increasing attention due to its superiority in 1) maintaining the distal gastric volume; 2) preserving the fundic gland area and reducing hormonal and nutritional deficiencies; and 3) ensuring the secretion of internal factors and gastric acid, the absorption of iron ions and vitamin B12, and the maintenance of hemoglobin concentration (3–6). However, the inevitable a loss of the antireflux barrier and postoperative complications resulting from proximal gastrectomy can severely affect the quality of life (7).

Recently, continuous improvements in digestive tract reconstruction after proximal gastrectomy have yielded the development of a variety of methods with antireflux functions that contribute to retaining the function of the residual stomach and avoiding serious reflux esophagitis (8–10). Japanese guidelines indicate that popular methods for gastrointestinal reconstruction after proximal gastrectomy include esophagogastrotomy (EG), jejunal interposition (JI), and double-tract reconstruction (DTR) (11–13). In 2016, Kuroda reported a double-flap technique using the anterior gastric wall plasma muscle flap to cover the anastomosis (14). Its unidirectional flap can reconstruct the “sphincter” and reduce the incidence of reflux esophagitis and the risk of anastomotic fistula.

By comparing patients who underwent direct esophagogastrostomy, jejunal interposition, double tract reconstruction, and the double-flap technique, Shoji Y (15) and Saze Z et al. (16) found that patients undergoing double-flap anastomosis had no reflux esophagitis and a lower incidence of postoperative anastomotic stricture, which improved postoperative serum albumin ratio changes and weight maintenance. Consequently, the double-flap technique is considered to be the most effective technique for proximal gastric reconstruction (17, 18).

However, the double-flap technique is associated with shortcomings, such as a more complex suture technique, more difficult operation, longer operation time and higher incidence of postoperative anastomotic stenosis (15, 16, 19). Therefore, our center attempted the left-open single-flap technique to reduce the difficulty of surgical suturing and the incidence of complications. To further evaluate the therapeutic efficacy of this procedure, we initiated a multicenter, prospective, randomized controlled trial for patients undergoing proximal gastrectomy, which will provide more evidence-based medical research for the development of clinical guidelines.

## Trial objectives

This study is a prospective, multicenter, randomized controlled clinical trial. We plan to recruit 250 patients who are eligible for proximal gastrectomy. After informed consent is obtained, patients will be randomly assigned to the trial group (left-open single-flap technique) and the control group (double-flap technique) in a 1:1 allocation ratio, with the aim of providing more evidence-based medical outcomes for digestive tract reconstruction in proximal gastrectomy. The surgical methods applied in this study are shown in **Table 1**.

**Table 1 T1:** Surgical methods applied in this study.

	Proximal gastrectomy	D2 lymphadenectomy	Left-open single-flap technique	Double-flap technique
The trial group	√	√	√	
The control group	√	√		√

The objectives of this trial are as follows:

### Main objective

The main objective is to investigate the incidence of reflux esophagitis after 2 types of anastomosis (left-open single-flap technique vs. double-flap technique) after proximal gastrectomy.

### Secondary objective

1) to investigate the incidence of anastomotic leakage of 2 types of anastomosis (left-open single-flap technique vs. double-flap technique) after proximal gastrectomy2) to investigate the incidence of anastomotic stricture of 2 types of anastomosis (left-open single-flap technique vs. double-flap technique) after proximal gastrectomy3) to investigate the operation time of 2 types of anastomosis (left-open single-flap technique vs. double-flap technique) after proximal gastrectomy4) to investigate the intraoperative blood loss volume of 2 types of anastomosis (left-open single-flap technique vs. double-flap technique) after proximal gastrectomy

## Prospective results

In patients after proximal gastrectomy, the left-open single-flap technique can decrease postoperative complications and increase nutritional status compared with the double-flap technique.

## Participant selection

The flow chart of this study is shown in **Figure 1**. During the routine admission of inpatients, suitable patients will be screened by the study staff according to the inclusion/exclusion criteria. Patients who are successfully selected before formal enrollment will receive study instructions from the investigator with a detailed explanation of the included documents and operations. Participants (or their legally authorized representative) will agree to sign and date the informed consent form after receiving a random serial number. All processes will strictly follow the provisions of the Ethical Review of Biomedical Research Involving Humans (Trial), the Declaration of Helsinki v.08, and the International Ethical Guidelines for Biomedical Research Involving Humans.

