## Blinding technique and randomization procedure

The study has an open design.

Before randomization, the oncologic evaluation will be performed based on relevant clinical parameters (vital signs, serum biochemical tests, tumor markers, CT and/or MRI, ultrasound endoscopy, etc.). Eligible participants will be informed by the investigator and required to sign an informed consent form. Patients will be randomly assigned in a 1:1 ratio to the trial group (left-open single-flap technique) and the control group (double-flap technique). The randomization sequence will be generated by a biostatistician using the SPSS 28.0.1 software. The randomization list will be sealed in an opaque envelope and placed in the custody of a dedicated person.

None of the assistants associated with the randomization process are directly involved in this study to avoid bias.

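### Participant selection has consent signed after the random number is received, while every other place that gives the order puts consent before allocation

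*Protocol article*

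**What the plan says.** The protocol article gives the order of consent and randomisation in five places.

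- **Participant selection:** participants "will agree to sign and date the informed consent form after receiving a random serial number". The number comes first, the signature second.
- **Abstract (Methods/design) and Trial objectives**, in the same words: "After informed consent is obtained, patients will be randomly assigned to the trial group". Consent comes first, explicitly.
- **Blinding technique and randomization procedure:** eligible participants are informed and "required to sign an informed consent form. Patients will be randomly assigned in a 1:1 ratio". Consent comes first by the sequence of the sentences, without the word *after*.
- **Table 3 (Clinical data collection):** written consent is ticked under Enrollment, the column to the left of Allocation.

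On blinding and concealment, the randomization section says "The study has an open design" and "The randomization list will be sealed in an opaque envelope and placed in the custody of a dedicated person". Signed consent is inclusion criterion 8, and refusal to sign is exclusion criterion 18.

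**The concern.** The sentence in Participant selection makes a positive statement about sequence, in the section that describes how a patient gets into the trial. Condensing a full protocol into an article does not explain it, because nothing has been left out. A step has been put in a different order.

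The order matters more here because the trial is open. If a number that discloses the arm is issued before the signature, patient and recruiter can know the reconstruction technique before the patient commits, and entry can then depend on the arm. The document gives a reason why a preference might exist. The Introduction calls the double-flap technique more complex and longer, with more stenosis, and the section Prospective results expects fewer complications with the single flap. Signing consent after allocation would also be a question for the ethics committee.

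**Working it through.** No figure in the plan depends on this point, so the check is a comparison of the text.

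**Step 1. Set the statements side by side.**

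| Place | Order stated | How it is stated |
|---|---|---|
| Abstract, Methods/design | consent, then assignment | explicit |
| Trial objectives | consent, then assignment | explicit |
| Blinding technique and randomization procedure | consent, then assignment | by sequence |
| Table 3 schedule | consent (Enrollment), then Allocation | by column |
| Participant selection | number, then consent | explicit |

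Four places agree and one is reversed. If the serial number is the randomisation number, the explicit statements cannot all be followed for the same patient.

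**Step 2. Ask what would happen if the reversed order were followed.** Two readings of the serial number are open.

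- *It is only an identification number, or the arm stays hidden until the sealed list is consulted.* Nobody learns the arm before consent. The wording is wrong, but no selection by arm follows.
- *It discloses the arm or lets it be known.* The sealed envelope no longer protects that patient once the number is issued, and the open design adds no further barrier. The arm can be known before consent.

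**Step 3. Under the second reading, trace a patient who declines.**

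- Inclusion criterion 8 (signed consent) is not met, and exclusion criterion 18 (refusal to sign) applies.
- Item 4 of Terminating criteria covers withdrawal only once the consent form has been signed, so it does not apply.
- The Follow-up section keeps patients who refuse follow-up in the analysis. It does not mention someone who never signed.

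No rule in the article would therefore count this patient as randomised, and the loss could go unseen.

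**Step 4. Ask whether the size can be computed.** That would need the number of refusals after a number was issued, by arm, and the reflux risk of those who refused. The document gives neither.

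**The case against.** The strongest reply is that this is a slip in one sentence. Four places agree on the accepted order, signed consent is an entry criterion, and the same section has the investigator inform patients before formal enrolment. The flowchart cited there is not reproduced in the text available and may settle the order. The sentence does not say that the number reveals the arm, the list is sealed with a dedicated person, and those who handle randomisation are kept apart from the study. All of this stands. It makes a drafting error the more likely explanation and any harm conditional. It does not remove the contradiction, and a site that followed the sentence literally would be following the published protocol.

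A reader might infer two stronger things, and the document supports neither.

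- **That allocation concealment is defeated, or that the investigators chose to randomise before consent.** This needs the number to disclose the arm, which is stated nowhere, and the rest of the document describes the opposite order.
- **That a handful of refusals would reverse the noninferiority conclusion.** Take 112 analysed per arm (125 less 10%, rounded down), 12 control events, and the upper one-sided 95% unpooled bound, d + 1.645 × √[p₁(1−p₁)/n₁ + p₂(1−p₂)/n₂], against the 10-point margin. Here 15 trial-arm events give 2.68 + 7.15 = 9.83 points (pass) and 16 give 3.57 + 7.26 = 10.83 (fail). But every fixed decision rule has a one-event edge. Refusal removes patients and adds no events. Starting from 12 against 12 (bound 6.80), remove four control patients who would all have had reflux. The comparison becomes 12/112 against 8/108: 3.31 + 6.35 = 9.65 points, still a pass. Five such patients, every one a future event, are needed to fail (12/112 against 7/107: 4.17 + 6.21 = 10.38). At an assumed 30% risk among five refusers the bound is 7.65. These event counts and risks are illustrative assumptions and do not measure this defect.

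**Conclusion.** The point holds as an internal inconsistency: Participant selection reverses the order of consent and randomisation given in the Abstract, Trial objectives, the randomization section and Table 3. The conflict in wording is certain. Selection by arm is only possible, and it rests on two assumptions: that the serial number discloses the arm or lets it be known, and that sites followed this sentence rather than the other four places. The size of any bias cannot be computed from the document. The sentence should be corrected and the records checked, because this is an entry rule in an open trial and the correction is cheap. Nothing here shows that the trial's conduct or its result is compromised.

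**What to change.** 1. Reword the sentence in Participant selection so that written consent is signed and dated before any randomisation number is requested or disclosed, in line with the Abstract, Trial objectives, the randomization section and Table 3. If the serial number is only an identifier, say so.
2. State that every patient with an issued allocation counts as randomised, including any who later decline, and report the number by arm.
3. Recruitment is stated to have started on August 1, 2022. For patients enrolled since then, compare the consent date with the allocation date, using times where both fall on the same day, and report any reversed order.

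The cost is one reworded sentence, one added sentence and a check of dates that should already be on file. The sample size, the endpoint and the analysis do not change.

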**Figure 1 f1:**
[figure not shown]
Flowchart of the trial.

### Inclusion criteria

1) patients aged 18-80 years, regardless of sex;2) Siewert III of esophagogastric junction adenocarcinoma: Stage I (cT_1-2_N_0_M_0_) or adenocarcinoma of the upper part of the stomach: Stage II (cT_1-2_N_0_M_0_), Stage II (cT_1-2_N_1-3_M_0_/cT_3-4_N_0_M_0_), Stage III (cT_3-4a_N_1-3_M_0_). All patients were selected according to the 8th AJCC clinical staging of gastric cancer.3) primary lesion diagnosed by preoperative endoscopic end pathology: tumor diameter <4 cm and located in the upper part of the stomach (including the esophagogastric junction), histologically confirmed adenocarcinoma;4) preoperative ASA score: I, II, or III;5) preoperative Karnofsky physical status score: ≥ 70%; or preoperative ECOG physical status score: ≤ 2;6) no distant metastases (confirmed by preoperative chest X-ray, abdominal ultrasound, and upper abdominal CT); No peritoneal implant metastases (confirmed by exploration surgery);7) R0 surgical outcome was expected to be obtained with D2 lymphadenectomy in radical proximal gastrectomy;8) patients and their families voluntarily participated in this study and signed the informed consent form after understanding the study content.

### Exclusion criteria

1) patients who have received any preoperative treatment, such as chemotherapy, radiotherapy, targeted therapy or immunotherapy; preoperative neoadjuvant chemotherapy recipients;2) patients with clinical stage exceeding Siewert III of the esophagogastric junction adenocarcinoma: Stage I (cT_1-2_N_0_M_0_) or more than adenocarcinoma of the upper part of the stomach: Stage I (cT_1-2_N_0_M_0_), Stage II (cT_1-2_N_1-3_M_0_/cT_3-4_N_0_M_0_), Stage III (cT_3-4a_N_1-3_M_0_);3) patients with acute infections, especially biliary tract infections;4) patients with complications of gastric cancer (bleeding, perforation, or obstruction) requiring emergency surgery;5) patients with uncorrectable coagulation dysfunction;6) patients with vital organ failure, such as heart, lung, liver, brain, kidney, etc.7) severe central nervous system disease, mental disorders, or impaired consciousness;8) pregnant or lactating women;9) patients with distant metastases;10) patients with a primary tumor at another site diagnosed within the past 5 years;11) preoperative ASA score: ≥ IV;12) preoperative ECOG physical status score: ≥ 2;13) history of continuous systemic corticosteroid therapy within the past 1 month;14) history of unstable angina, myocardial infarction, cerebral infarction, or cerebral hemorrhage within the past 6 months;15) patients with concurrent surgical treatment of other diseases;16) patients with immunodeficiency, immunosuppression, or autoimmune diseases (organ transplant requiring immunosuppressive therapy within the past 5 years, allogeneic bone marrow transplant patients, taking immunosuppressive drugs, etc.);17) patients with concurrent participation in other clinical studies;18) patients refusing to sign an informed consent form to participate in this study;19) preoperative imaging: regional fusion of enlarged lymph nodes (maximal diameter > 3 cm).

### Terminating criteria

1) patients are inoperable for various reasons after recruitment;2) the investigator considers that the patient should stop this study for safety reasons or the benefit of the patient;3) serious complications or intolerable adverse reactions of the patient;4) patients may request to withdraw/terminate from the trial at any time after signing the informed consent form.

### Rejecting criteria

1) patients with missing main observation indicators and significantly incomplete study data;2) incomplete follow-up data;3) patients who failed to follow the study protocol;4) the study protocol was discontinued after the patient was judged to be a culled case. Follow-up treatment was determined by the investigator according to clinical guidelines. The excluded cases were still subject to follow-up and were included in the study analysis.

## Blinding technique and randomization procedure

The study has an open design.

Before randomization, the oncologic evaluation will be performed based on relevant clinical parameters (vital signs, serum biochemical tests, tumor markers, CT and/or MRI, ultrasound endoscopy, etc.). Eligible participants will be informed by the investigator and required to sign an informed consent form. Patients will be randomly assigned in a 1:1 ratio to the trial group (left-open single-flap technique) and the control group (double-flap technique). The randomization sequence will be generated by a biostatistician using the SPSS 28.0.1 software. The randomization list will be sealed in an opaque envelope and placed in the custody of a dedicated person.

None of the assistants associated with the randomization process are directly involved in this study to avoid bias.

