## Sample size estimate and statistical analysis

The left-open single-flap technique after proximal gastrectomy is a new and improved procedure in our center, and national or international studies comparing clinical outcomes after reconstruction with the double-flap technique have not been conducted. Kuroda S et al. (22) showed that the incidence of reflux esophagitis, performed by endoscopy at 1.0 years (median) after the double flap technique, was 10.6% for all grades. This finding was considered more in line with “real‐world data”.

According to the database of this study, we designed a noninferiority study with a noninferiority margin of 10% (α=0.05, β=0.20, δ =0.10, 80% power, 10% dropout rate). The test statistic used is the one-sided Z test (unpooled) by PASS 15.0.5 software.

The result is N = 250. Therefore, 125 patients will be enrolled in each of the 2 groups.

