### Primary study endpoints

1) Incidence of reflux esophagitis (22);

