## Follow-up

The start time of this study was August 1, 2022. The preliminary completion time is July 31, 2024. Follow-up will be planned for three years, and the study completion time will be July 31, 2027.

Esophagogram fluoroscopy will be performed 6 days after surgery to evaluate anastomotic complications. Subsequent follow-ups will be performed at 1, 3, 6, 12, 24 and 36 months. The follow-up will include questioning, physical examination, gastrointestinal endoscopy, blood examination items (peripheral blood routine, serum iron, vitamin B12, folic acid, blood biochemistry and serum tumor markers), and imaging items (chest imaging, esophagogram fluoroscopy, and whole abdomen enhanced CT). All examinations will be recorded to evaluate the presence of tumor recurrence or metastasis, the survival status of patients and the occurrence of complications. Other assessment tools will be used according to the specific situation, such as color ultrasound of other sites, whole-body bone scan, PET-CT, etc. The follow-up schedule in this study is shown in **Table 3**.

The diagnosis of postoperative reflux symptoms is based on a combination of symptom presentation, endoscopic evaluation of esophageal mucosa, reflux monitoring, and response to therapeutic intervention (23–25). Heartburn and regurgitation remain the typical symptoms of postoperative reflux symptoms. The control steps of postoperative reflux symptoms are shown in the **Table 4**.

**Table 4 T4:** The control steps of postoperative reflux symptoms.

Management	Nonpharmacologic lifestyle modifications	Weight managemen	1. Weight loss in overweight and obese patients for improvement of postoperative reflux symptoms. 2. For the patients with regurgitation or belch predominant symptoms; but we do not recommend baclofen in the absence of objective evidence of postoperative reflux symptoms.
		Body positioning	1. Elevating the head of the bed. 2. Staying upright during and after meals.
		Diet modification	1. Avoidance of “trigger foods”. 2. Avoiding meals within 2–3 hours of bedtime. 3. Tobacco and alcohol cessation. 4. Avoidance of late night meals and bedtime snacks.

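### The open design makes no exception for the assessor of reflux esophagitis, and any under-reading confined to the trial arm would favour the non-inferiority claim

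*Protocol article*

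**What the plan says.** The section on blinding and randomization in the protocol article makes one statement about masking: "The study has an open design". It goes on to keep the staff who handle randomization apart from the study, as a guard against bias, but gives no similar protection to outcome assessment. No other section describes a masked, central or independent reading.

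The primary endpoint is listed as "Incidence of reflux esophagitis (22", the number being a literature reference. No grade threshold or assessor is given. The sample size section takes its control rate from a published double-flap series assessed by endoscopy, where the incidence "was 10.6% for all grades". It specifies "a noninferiority margin of 10% (α=0.05, β=0.20, δ =0.10, 80% power, 10% dropout rate" and adds: "The test statistic used is the one-sided Z test (unpooled) by PASS 15.0.5 software".

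The Follow-up section lists gastrointestinal endoscopy among the follow-up examinations. It says that a follow-up specialist records results, and it accepts re-examination at outside tertiary hospitals.

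**The concern.** Surgeons cannot be masked to the reconstruction they perform, so an open trial is a natural label. That does not require the person who grades the esophagus to know the arm. Mild mucosal change is where grading depends most on judgement, and the planning rate counts it.

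The direction matters as well. The technique comes from the lead center. The article predicts fewer complications with it (Prospective results) and reports favourable preliminary experience (Discussion). In a superiority trial, expectations of this kind would have to create a difference. Here they need only shrink one: each trial-arm case that goes unrecorded brings the observed difference further inside the margin. The stake is a non-inferiority claim for a technique whose true excess of esophagitis is as large as the margin.

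**Working it through.** **Inputs from the article (sample size section).** Control rate 10.6%; margin 0.10; one-sided alpha 0.05; power 80%; dropout 10%; unpooled Z test; 125 enrolled per arm.

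**Input that is assumed.** The fraction u of true trial-arm cases that is missed, with none missed in the control arm. The article gives no figure, so u runs from 0 to 20%.

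**The plan's own sample size first.** n per arm = 2p(1−p)(1.645 + 0.842)² / 0.10².
- p = 0.106: n = 117.2, so 118. Then 118/0.9 = 131.1, so 132 per arm and 264 in total, not 250.
- p = 0.10: n = 111.3, so 112. Then 112/0.9 = 124.4, so 125 per arm and 250 in total.

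The stated 250 is therefore what a control rate rounded to 10% gives. That is a separate matter and does not affect the result below. Evaluable patients: 125 × 0.9 = 112.5, taken as 112 per arm.

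**False non-inferiority rate.** Put the truth on the margin: control 0.106, trial 0.106 + 0.10 = 0.206. The observed trial rate is pT = 0.206(1 − u). Non-inferiority is declared when the observed difference plus 1.645 standard errors is below 0.10. By normal approximation:

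P = Φ( (0.206 − pT)/SE − 1.645 ), with SE = √{[0.106 × 0.894 + pT(1 − pT)]/112}.

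Example, u = 10%: pT = 0.1854; SE = √[(0.0948 + 0.1510)/112] = 0.0469; (0.0206/0.0469) − 1.645 = −1.205; P = 11.4%. The exact rate sums the binomial probabilities of all pairs of counts for which the test declares non-inferiority.

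| Trial-arm cases missed (assumed) | Observed trial rate | Approximate | Exact |
|---|---|---|---|
| 0% | 20.60% | 5.0% | 5.2% |
| 5% | 19.57% | 7.7% | 8.0% |
| 8% | 18.95% | 9.8% | 10.1% |
| 10% | 18.54% | 11.4% | 11.8% |
| 15% | 17.51% | 16.5% | 16.9% |
| 20% | 16.48% | 23.0% | 23.5% |

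With all 125 per arm evaluable, the exact figures are 5.4%, 8.4%, 12.7% and 25.7% at 0%, 5%, 10% and 20%.

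**Reading the table.** The rate about doubles at 8% missed. That is 0.08 × 20.6 = 1.6 percentage points, or about 2 of the 23 cases expected among 112 patients (0.206 × 112 = 23.1). At 5% the rise is about 1.5-fold (8.0/5.2).

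**What masking can and cannot do.** If it removed the differential entirely, the rate would return to 5.2%. It does not touch under-reading shared by both arms: 10% missed in each gives observed rates of 9.54% and 18.54% and an exact rate of 8.1%, because the margin is a fixed absolute difference.

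**The case against.** The size and direction of misreading are assumed. The calculation combines true rates exactly on the margin with misses in one arm only. A new technique might equally be scrutinised more closely; over-calling in its arm would work against the claim. Nothing says that surgeons or developers grade the endoscopies. The article condenses a fuller protocol that may name a masked assessor. All of this stands as a limit on what can be asserted: the figures show sensitivity and do not predict bias. It does not remove the point, because the section devoted to blinding declares the whole study open without qualification.

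Four stronger readings are tempting and are not supported.
- *Masking is free.* The article names no endoscopist. The two anastomoses differ visibly (stapled under a single flap, hand-sewn under a double flap), the patient knows the operation, and outside-hospital examinations are allowed.
- *The endpoint is esophagitis of any grade.* That wording belongs to the planning rate; the endpoint line gives no grade.
- *The endpoint also counts symptoms and treatment response.* The Follow-up section does refer to "symptom presentation, endoscopic evaluation of esophageal mucosa, reflux monitoring, and response to therapeutic intervention", but as the basis for diagnosing postoperative reflux symptoms, not esophagitis.
- *Any modest under-reading more than doubles the error.* This is true only from about 8% upward, and only if the misses are confined to the trial arm.

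**Conclusion.** The point holds in limited form. The article fixes an open design without exempting the assessor of an endpoint that involves judgement, in a test where under-reading of the new arm helps the claim. With the truth on the margin and 112 evaluable per arm, the false non-inferiority rate is 5.2% without misreading and between 8.0% and 23.5% when 5% to 20% of trial-arm cases alone are missed. Those fractions are not from the documents, and no bias has been shown. Masking the assessor where feasible is a worthwhile, inexpensive improvement. It gives partial protection, and the open label does not by itself invalidate the trial.

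**What to change.** In the blinding section, replace the unqualified statement with: open for surgeon and patient; the assessor of the primary endpoint is masked where feasible. Specify that the endoscopist performing the follow-up endoscopy listed in the Follow-up section:

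1. is not a member of the operating team;
2. is not told the arm on the endoscopy request;
3. records the esophagitis grade before describing the anastomosis.

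The schedule table marks endoscopy at baseline only, so it should be reconciled with the Follow-up section in the same amendment.

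Cost: a change to the request form and some care in assigning endoscopists. Sample size and procedures are unchanged, and no additional reader is required. Downsides: the anastomosis or the patient may reveal the arm, examinations at outside hospitals are harder to control, and under-reading common to both arms remains. Masked reading of stored esophageal images would be a firmer safeguard, but it needs a further reader and is not essential to this change.
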